#### Statistics

For the primary outcome, we will describe the proportion of ICUs that achieved ≥ 80% of all three indicators (fidelity, reach and adoption). We will also report these indicators separately. We will compare the proportion achieved in the post-implementation period, as specified in the Table 2, with the baseline assessment, using a McNemar test (Chi-square for repeated measures).

**Table 2 Tab2:** Outcomes

**Outcome**	**Measure and reporting**
Implementation (Primary Outcome)	**Fidelity: **The proportion of prescriptions reviewed as intended (review at 48hrs with documentation of all 4 review components: indication, route, duration and stop date). Reported as a proportion of the number of possible reviews during months 4-6. Numerator: Number of reviews conducted as intended Denominator: Number of prescriptions of antimicrobials Expressed as a %. Binary outcome: success/fail, 80% is threshold. Proportion of weekly A&F report meetings held from month 4 until the time of adoption (Number of meetings/12, expressed as a %) (not in composite outcome)
	**Reach: **Proportion of eligible patients who received a review during months 4-6 Numerator: Number of patients that received at least 1 prescription review Denominator: Number of eligible patients Expressed as a % Binary outcome: success/fail, 80% is threshold. Proportion of eligible staff that receive education (expressed as a %; eligible staff defined prospectively by Champion) (not in composite outcome)
	**Adoption**: Proportion of prescriptions reviewed as intended during month 7 Numerator: Number of prescriptions of antimicrobials reviewed Denominator: Number of prescriptions of antimicrobials Expressed as a % Binary outcome: success/fail, 80% is threshold.
Intervention effectiveness (secondary outcomes)	**Appropriateness of prescriptions:** Antimicrobial Density (AD) Duration of Therapy (DOT) Antimicrobial Redundancy Rate (ARR)
	**Antimicrobial care processes:** Does the drug Duration exceed the Stop date? Antimicrobial resistance rate (% of patients that have an multidrug resistant pathogen identified) Antimicrobial prescribing rate (% of all patients) Count of cultures taken and reported as a proportion of the population on antimicrobials.

For the secondary outcomes, we will perform an interrupted times series analysis. We will observe the weekly temporal resolution of each indicator and set the model to account for the natural/secular time trend, implementation of the intervention (level change) and the trend after implementation (slope change). We will account for auto-correlations. The model applied will depend on the data, but we will evaluate ARIMA models, segmented regressions and Holt-Winters additive model to evaluate the best model for the times series. Counts of actions recorded in response to the review will be described. The code lists for the primary and the secondary outcomes, and definitions for indicators of quality will be developed and published in advance of data collection.

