### Site selection criteria

All adult ICUs within CCAA-affiliated CQRs, where surveillance of antimicrobial utilisation has already been established will be considered for participation. ICUs must appoint a named Champion in order to participate. A survey (Supplementary File 2) will be conducted to determine pre-existing AMS processes and current adoption of structured review activities. Pre-existing antimicrobial review processes are neither a requirement for an ICU to participate nor an exclusion criterion. Instead, parallel to the survey, pre-implementation patient-level data pertaining to current antimicrobial prescribing review practices will be measured during months 1–2. ICU’s which are found to already have a structured antimicrobial review in place, and which demonstrate adoption and reach of 80% or greater (median over the 2 months) will not be eligible to participate in the implementation. This is because the baseline activity will confound the selected measures for implementation success. However, findings of the project will be shared with those ICUs, along with opportunities to participate in subsequent improvement activities.

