### Outcomes

#### Primary outcome: implementation

Implementation is the primary outcome and will be assessed quantitatively using 3 of the 5 key domains identified through the RE-AIM framework: Reach, Implementation (defined as fidelity) and Adoption (see Table 1). These will be combined into a composite measure of implementation with a threshold of 80% for success in each domain. Furthermore, Champions’ perceptions of the determinants of successful implementation, including acceptability, maintenance of, and adaptations to, implementation will be captured through field notes and interviews [51].

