### Data collection

Data regarding case mix (including source and reason for admission, severity of illness at admission, comorbidities) along with physiology, organ support, antimicrobial prescriptions and microbiology data, care processes (duration of antimicrobials) and clinical outcomes will continue to be collected daily through the existing CQR during months 1–8. The CQR data collectors will also collect adoption and reach of any pre-existing structured review during months 1–2.

A project specific E-CRF on REDcap [52, 53], will capture data on antimicrobial reviews during months 4–6 (see Table 1 above). This additional E-CRF collection will be done by the RAs. Copies of existing antimicrobial guidelines will be requested prior to commencement of the study, and ICU stakeholders’ perspectives regarding the current guidelines, along with information on existing antimicrobial stewardship activities already present in the ICU captured during the site onboarding by Champions. Changes in guidelines made during the project will also be captured, and the current working version of the guidelines queried at each phase of the project. Post implementation (months 7 onwards), the CQR data collection will continue, along with a measure of adoption.

Qualitative data exploring the Champions’ perspectives regarding implementation, acceptability, adoption and maintenance, along with contextual factors influencing implementation will be collected through semi-structured interviews at two time points during the study: implementation (months 4–6) and post-implementation (month > 6). We intend to interview all Champions during both phases but recruitment may cease if concurrent analysis indicates that theoretical saturation has been achieved. Interviews will be conducted remotely using the Zoom (Zoom Video Communications Inc, San Jose, CA, USA) conferencing application. A participant information sheet (Supplementary File 5) will be provided and verbal consent for participation sought (Supplementary File 6). In addition, Champions together with RAs will be requested to maintain an implementation log [54], whereby adaptations, and observed barriers and facilitators to implementation will also be reported. These will be reviewed and thematically coded alongside the interview data.

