### Analysis

All analysis will be conducted at the level of ICUs. ICUs will be identifiable only by their type (i.e. medical, surgical, mixed or speciality), and by their organisation governance type (private, public, other). ICUs who have a pre-existing structured review with an adoption rate of 80% will be included in the context description, but not in the intervention analysis described below. No country or regional level analysis is planned. However participating CQRs will have access to their sites’ data for subsequent evaluation once the primary outcome is published.

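### The McNemar test against baseline is uninformative on the composite primary outcome, because the exclusion rule leaves no, or almost no, ICU that could be a success at baseline

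*Protocol article*

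**What the plan says.** The primary outcome is a "composite measure of implementation with a threshold of 80% for success in each domain" (Primary outcome: implementation). Under Statistics, the result is the proportion of ICUs at or above "80% of all three indicators (fidelity, reach and adoption"), with each indicator also reported on its own. The next sentence adds the comparison with baseline: "We will compare the proportion achieved in the post-implementation period, as specified in the Table 2, with the baseline assessment, using a McNemar test". No significance level, test variant or required share of successful ICUs is given.

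Two sections decide which ICUs enter that comparison.

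- Site selection criteria: the rule concerns ICUs where a structured review is already running. Those "which demonstrate adoption and reach of 80% or greater (median over the 2 months) will not be eligible to participate in the implementation". The stated reason is that baseline activity would confound the measures of implementation success.
- Analysis: "ICUs who have a pre-existing structured review with an adoption rate of 80% will be included in the context description". The same sentence leaves these ICUs out when the intervention is analysed. Reach is not mentioned here.

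On baseline data, Data collection states: "The CQR data collectors will also collect adoption and reach of any pre-existing structured review during months" 1 and 2. Table 2 measures fidelity and reach over months 4 to 6, and adoption in month 7.

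**The concern.** A McNemar test compares the units that change in one direction with those that change in the other. It is informative when both directions are possible. Here an ICU that met the composite at baseline would have adoption and reach at 80% or more, and those are the ICUs that the exclusion removes. Movement from success to failure is then ruled out by design, or nearly so, and any few ICUs that succeed afterwards produce a small p-value.

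The project's hypothesis is that the review can be implemented to thresholds set in advance. A p-value that is small when most ICUs miss those thresholds does not bear on that hypothesis, yet it is the only inferential result the plan attaches to the primary outcome. A reader of the final report could easily give it more weight than it carries.

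**Working it through.** **Inputs.** Number of ICUs: 35 (Abstract), with 35 to 40 anticipated (Recruitment). Success: all three indicators at 80% or more. Exclusions: as quoted above, reading the Analysis wording as 80% or more. Significance level: not stated, assumed two-sided 0.05. Variant: not stated, so several were computed.

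**The plan's own figure.** No size calculation is given for this test. The only size figure is the encounter count, which reproduces: 40 × 0.75 × 6 = 180 per ICU, and 180 × 35 = 6300.

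**Step 1, the baseline count.** Composite success at baseline requires adoption ≥ 80% and reach ≥ 80%. That meets the exclusion in Site selection criteria, and the one in Analysis as well. Let b be the ICUs going from success to failure and c those going from failure to success. Then b = 0.

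**Step 2, the test with b = 0.**

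- Uncorrected: χ² = (c − b)²/(b + c) = c
- Continuity-corrected: χ² = (|c − b| − 1)²/(b + c) = (c − 1)²/c
- Exact: p = 2 × 0.5^c

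| Successful ICUs (c) | Share of 35 | Uncorrected p | Corrected p | Exact p |
|---|---|---|---|---|
| 3 | 8.6% | 0.083 | 0.248 | 0.250 |
| 4 | 11.4% | 0.046 | 0.134 | 0.125 |
| 5 | 14.3% | 0.025 | 0.074 | 0.063 |
| 6 | 17.1% | 0.014 | 0.041 | 0.031 |

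The cut-off is 4 ICUs (uncorrected) or 6 (corrected or exact). The mid-p version falls between, at 5 (p = 0.031). The total number of ICUs does not enter any formula, so with 40 ICUs the same counts are 10% to 15%.

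**Step 3, what such a result would mean.** Exact 95% confidence intervals: 4/35 = 11.4% (3.2% to 26.7%); 6/35 = 17.1% (6.6% to 33.6%). Treating ICUs as independent, the chance of significance with 35 ICUs is:

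| True share of ICUs succeeding | Cut-off 4 | Cut-off 6 |
|---|---|---|
| 10% | 47% | 13% |
| 20% | 94% | 73% |
| 30% | 99.8% | 97% |

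**Step 4, sensitivity.** At an assumed two-sided 0.01 the cut-off is 7 (uncorrected), 8 (exact) or 9 (corrected). If one borderline ICU did count as a baseline success and later failed (b = 1), the cut-off at 0.05 becomes c = 7 (uncorrected, p = 0.034) or c = 8 (corrected p = 0.046; exact p = 0.039), which is 20% to 23% of 35.

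**Step 5, the single indicators.** The exclusion in Analysis removes every ICU with baseline adoption of 80%, so baseline adoption successes are zero. Fidelity counts only prescriptions reviewed as intended, over all prescriptions. Over the same period it cannot exceed the share reviewed at all, so fidelity of 80% implies adoption of 80%, and the same zero follows. Reach differs: an ICU with reach of 80% or more but adoption below 80% stays in under both rules.

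**Step 6, the two rules.** An ICU with baseline adoption of 80% or more but reach below 80% may take part under Site selection criteria, yet is left out of the intervention analysis under Analysis. The two sections define different sets.

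**The case against.** The strongest reply is that the test is not the primary analysis. Success is defined ICU by ICU, and the first stated result is a description of how many ICUs achieved it. If 4 of 35 succeed, the headline is 11%, whatever the p-value. This stands. A reader might infer that the trial would declare success on a significant McNemar result while 29 to 31 of 35 ICUs failed. The protocol does not say that: it sets no alpha, and nowhere makes the p-value the decision rule.

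Second, an exact zero is slightly firmer than the text. Eligibility uses a median over months 1 and 2, while baseline collection runs over months 1 to 3 (Implementation procedure), so a borderline ICU could count as a baseline success on pooled data. The sentence may also be meant for single indicators, and reach then need not start at zero. Both stand as small exceptions. Neither makes the composite test informative.

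Two further inferences fail. A reader might conclude that the baseline composite cannot be measured, because fidelity is not named among the baseline items. But an ICU that fails adoption or reach has failed the composite whatever its fidelity. A reader might also see a conflict between Implementation procedure, which lists the E-CRF among baseline sources, and Data collection, which places the E-CRF review data in months 4 to 6. The first concerns utilisation and prescribing appropriateness and the second concerns reviews, so both can be true.

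Finally, the test variant and alpha may be set in an analysis plan that is not shown. That would fix the cut-off within the range above, but would not restore the missing baseline successes.

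**Conclusion.** The point holds as an uninformative test attached to a sound descriptive primary result. On the composite reading, baseline successes are zero or nearly so, and significance at an assumed two-sided 0.05 needs only 4 to 6 successful ICUs, or 11% to 17% of 35. The range reflects the unstated variant. The conclusion rests on reading the compared proportion as the share of ICUs achieving all three indicators, which is the natural reading, and on the exclusions being applied as written. The definition of success, the estimated proportion and the planned data collection are unaffected.

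**What to change.** 1. Remove the McNemar comparison for the composite, and for adoption and fidelity, where the exclusion in Analysis forces the same zero.
2. Report the number of ICUs achieving all three indicators with an exact 95% confidence interval. A share of ICUs that would count as enough could be fixed in advance, but this is optional.
3. Show change from baseline as the paired within-ICU difference, with a confidence interval, in the continuous rates measured in both periods: adoption in months 1 and 2 against month 7, and reach in months 1 and 2 against months 4 to 6. State alongside it that selecting ICUs below 80% at baseline may favour apparent improvement.
4. Use one exclusion rule in Site selection criteria and in Analysis, so that the ICUs taking part and the ICUs analysed are the same set.

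The cost is wording only, since these rates are already to be collected. What is lost is an easy p-value.

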#### Conduct of review

Participating ICU teams will be required to undertake a structured review of each antimicrobial prescription for all patients receiving antimicrobials. Reviewing prescriptions allows their appropriateness to be reconsidered in the context of emerging clinical and/or microbiological data [37]. The review should be completed within 48 h of a new prescription being commenced, or at ICU admission where pre-ICU antimicrobial prescriptions exist. The review will necessitate documentation of the four key steps as defined by the WHO: indication (in relation to pre-existing local guidelines), route (e.g. parenteral or enteral), expected duration of therapy and intended stop date (including escalation or de-escalation discussions). It will also necessitate documentation of any changes (or lack thereof) made to the prescription, including: the choice of drug, route of administration and duration of treatment. The reviewing ICU team will consider the choice of therapy in relation to the known or assumed indication, the dose in relation to local ICU antimicrobial guidelines, the route of administration, and whether escalation to parenteral, or de-escalation to enteral route (and related dosing and duration adjustments) are warranted. Given the rapidly changing clinical status of critically ill patients, and emerging clinical and/or microbiological data during the ICU stay, it is anticipated that patients may receive more than one review during their ICU encounter. ICUs’ existing antimicrobial guidelines for the management of infections in critically ill patients will be utilised.

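### The Fidelity row of Table 2 uses three bases that do not agree, so this component of the primary outcome has no single value to set against the 80% threshold

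*Protocol article*

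**What the plan says.** The Fidelity row of Table 2 (Statistics section) makes three statements about one quantity:

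- The definition: "The proportion of prescriptions reviewed as intended (review at 48hrs with documentation of all 4 review components: indication, route, duration and stop date".
- The reporting base, and after it the fraction: "Reported as a proportion of the number of possible reviews during months 4-6. Numerator: Number of reviews conducted as intended Denominator: Number of prescriptions". The prescriptions in the denominator are the antimicrobial ones.

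The row then applies a cut: "Binary outcome: success/fail, 80% is threshold". The text above the table counts an ICU as successful only if fidelity, reach and adoption all reach 80%.

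Timing is stated in two places. Table 2 requires a "review at 48hrs with documentation of all 4 review components". The Conduct of review section asks for completion within 48 hours of the start of a new prescription, "or at ICU admission where pre-ICU antimicrobial prescriptions exist". The same section says that "it is anticipated that patients may receive more than one review during their ICU encounter", and Strategy 1 lets each ICU set how often reviews happen beyond the 48-hour one.

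The Adoption row has prescriptions both above and below the line. Its definition asks for review as intended, but its numerator asks only for review.

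**The concern.** The definition counts prescriptions. The reporting line counts opportunities for review. The fraction counts reviews over prescriptions. A programmer could follow any of the three, and they coincide only if each prescription has exactly one possible review and contributes at most one qualifying review.

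The two timing readings expose different weaknesses:

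- **Within 48 hours.** More than one complete review of the same prescription can fall inside the window. The Conduct of review section expects existing daily ward rounds to be used, so two reviews on successive days are plausible. The ratio can then be too high.
- **Exactly at 48 hours.** A prescription that stops earlier, or whose patient dies or leaves earlier, stays in the denominator and cannot succeed. A pre-ICU prescription already past 48 hours on arrival is in the same position, and the Rationale section says prescriptions often start before ICU admission. The ratio can then be too low.

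Fidelity is cut at 80% and feeds an all-three rule, so the choice of base can change the primary result of an ICU near the threshold.

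**Working it through.** **The plan's own figures.** The Recruitment section gives a median of 40 admissions per month, 75% of them on antimicrobials, over 6 months and 35 ICUs. 40 × 0.75 × 6 = 180 encounters per ICU, and 180 × 35 = 6300. Both agree with the stated figures.

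**Scale for Fidelity.** Months 4–6 give 40 × 0.75 × 3 = 90 treated patients per ICU. At one prescription per patient (assumed), 0.80 × 90 = 72 must be reviewed as intended.

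**Notation.** The documents give none of these values, so ranges are assumed.

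- e: share of prescriptions for which no qualifying review is possible
- f: share of the remaining prescriptions that are reviewed as intended
- r: extra qualifying reviews per reviewed prescription

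The fraction as printed equals f × (1 − e) × (1 + r).

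**Repeats only (e = 0).** The share of prescriptions that must be reviewed to pass is 0.80/(1 + r):

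- r = 0.10: 72.7%
- r = 0.20: 66.7%
- r = 0.25: 64.0%
- r = 0.50: 53.3%

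At r = 0.20, for example, 60 of 90 prescriptions yield 60 × 1.20 = 72 reviews, and 72/90 = 80%. An ICU that reviews 70% of prescriptions scores 0.70 × (1 + r), which is 77%, 84%, 87.5% and 105% at the same four values. The last shows that the ratio is not bounded at 100%.

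**Unreviewable prescriptions only (r = 0).** The highest attainable score is 1 − e, and the rate needed on the rest is 0.80/(1 − e):

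- e = 5%: 84.2%
- e = 10%: 88.9% (72 of 81 when 9 of 90 cannot be reviewed)
- e = 15%: 94.1%
- e = 20%: 100%
- e = 25%: 106.7%, not attainable

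An ICU with f = 90% scores 85.5%, 81.0%, 76.5% and 72.0% at e = 5%, 10%, 15% and 20%. It passes at the first two and fails at the last two.

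**Both together.** The effects oppose each other and can cancel. At e = 20% and r = 0.25, (1 − 0.20) × (1 + 0.25) = 1, and the printed fraction returns f.

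**Limiting the denominator to prescriptions still active at the end of the window.** Take 90 prescriptions with 72 reviewed as intended, which is 80%. Suppose 9 of the 72 were stopped inside the window because of the review (assumed). The restricted figure is (72 − 9)/(90 − 9) = 63/81 = 77.8%. The ICU now fails because its reviews led to early stops.

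**The case against.** The best defence is that the row opens with a clear prescription-level definition and the rest is loose shorthand. Review as intended is tied to the 48-hour review with all four components, so later repeats need not qualify. The expectation of more than one review is stated per patient encounter, and a patient with several prescriptions would properly have several reviews. Table 1, Strategy 2 and the Conduct of review section all speak of within 48 hours, so the Table 2 timing may be a slip. Because every prescription is to be reviewed, each can be read as one possible review. The Statistics section also promises code lists and definitions before data collection.

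Much of this stands, and it rules out three stronger readings that a reader might infer:

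- **That repeat reviews do inflate Fidelity.** They do so only if more than one review of the same prescription counts as the 48-hour review. The text allows this but does not establish it.
- **That 80% cannot be reached.** With no repeat counting, this needs more than 20% of prescriptions to be unreviewable, and the documents state no such share. Under the within-48-hours wording, an early stop does not by itself prevent a review.
- **That ICUs would in effect be ranked by length of stay.** The plan ranks nothing on Fidelity, and the documents offer no figure for a case-mix effect.

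The defence does not remove the contradiction. The explicit numerator and denominator are what a programmer would implement, and they differ from the definition in the same cell. The promised code lists would still have to choose between conflicting published definitions of a primary-outcome component, which is more than filling in detail.

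**Conclusion.** The point holds as an internal contradiction in a component of the primary outcome. Three bases are given for Fidelity, and the one written as a fraction is not a proportion. The timing of a qualifying review also differs between Table 2 and the Conduct of review section.

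The size is conditional. If repeats qualify, the share of prescriptions needed to pass falls to 0.80/(1 + r), which is 67% at an assumed r of 0.20. If unreviewable prescriptions stay in the denominator, the rate needed on the rest rises to 0.80/(1 − e), which is 89% at an assumed e of 10%. The second effect matters mainly if review at 48 hours is read literally. Which effect dominates cannot be told from the documents. Either can reverse the result of an ICU near 80%.

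**What to change.** - **Fidelity.** Use the prescription as the unit throughout and count each at most once. Numerator: prescriptions with at least one review as intended. Denominator: all antimicrobial prescriptions in months 4–6, which matches the requirement to review every prescription. Delete the reference to possible reviews or define it to mean the same thing.
- **Timing.** Reconcile Table 2 with the Conduct of review section, including when the clock starts for pre-ICU prescriptions. The choice of window is the sponsor's.
- **Adoption.** Use the same as-intended numerator, so that it agrees with the row's own definition.
- **Sensitivity analysis.** Report Fidelity among prescriptions still active, with the patient still in the ICU, at the end of the window. It should not be the main figure, because it drops prescriptions that were reviewed and appropriately stopped early, and the Rationale section names avoidance and de-escalation among the purposes of the review.

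This removes r and caps the main figure at 100%. It does not remove e; comparison with the sensitivity analysis indicates how much e may matter.

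The cost for Fidelity is a rewording of Table 2 and one counting rule. The sensitivity analysis needs prescription and ICU stay dates; the registry already collects prescriptions, antimicrobial duration and clinical outcomes daily. Adoption may cost more. After month 6 the registry data collectors take over auditing whether reviews take place, and they would also have to record timing and the four components during month 7.

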### Implementation

#### Design

A multifaceted approach has been shown to be a critical condition for success of implementation in various settings [39]. Combining implementation strategies has been demonstrated to have a greater success of both implementation and intervention effectiveness when compared to the use of single strategies alone [40]. This project will combine three implementation strategies that have been reported to have been both effective in implementing practice change in critical care in LMICs in a recent systematic review [39], and leverage existing infrastructure already operational in the CQR networks [41, 42]. These strategies are described below and summarised in Table 1.

**Table 1 Tab1:** Implementation strategies

QI strategy	Description
1 Protocolised review	Agreement and documentation of a local protocol for structured antimicrobial review (‘the intervention’) in the ICU
2 CQR enabled audit and feedback	CQR report of audit data on implementation of the prescribing review and on prescribing indicators will be available to each ICU. The A&F implementation strategy will augment the existing audit and feedback mechanism which is part of CQR participation. **The existing monthly CQR report has data on:** Proportion of patients receiving one or more antimicrobials (APR), Duration of therapy (DOT) Case mix, care processes and clinical outcomes (Length of Stay, Mechanical Ventilation, mortality). **Additional data collected for audit throughout the project:** Proportion of prescriptions with a documented indication Antimicrobial Density (AD) Culture rates Antimicrobial resistance rates Antimicrobial redundancy rates (as a proportion of total prescriptions). **Additional data collected for audit and feedback weekly during months 4–6:** Proportion of prescriptions reviewed Proportion of reviews within 48 h of prescription commencement Proportion of prescriptions with a documented indication Antimicrobial Density (AD) Proportion of patients with culturing performed Antimicrobial resistance rates (as a proportion of cultures performed). **Ongoing additions to monthly CQR reports beyond month 6** Proportion of prescriptions reviewed

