Audit and feedback for the project will augment an existing CQR report whereby data on case mix, clinical outcomes, and proportion of patients receiving antimicrobials, along with the following measures of antimicrobial utilisation are reported monthly: Antimicrobial Density (AD), culture availability, Duration of Therapy (DoT) and Antimicrobial Resistance Index (ARI). More details on this dataset are published [42, 45, 46]. For the duration of the project (7 months), existing antimicrobial utilisation reporting will be augmented by the measurement and reporting of antimicrobial redundancy rate. Once structured prescribing review commences, the proportion of eligible patients receiving a prescribing review within 48 h will also be reported, along with each ICU’s performance on the 4 components of the review (indication appropriateness, route, duration and stop date) compared to other participating sites. Data on indications and microbiology data will also be captured and reported. Following commencement of the review, frequency of reports will be increased to weekly (for a maximum of 3 months). Champions will be encouraged to facilitate review of the report and discussion of the audit data with the wider ICU team, at their preferred frequency and structure, but as a minimum weekly. The presence, format and structure of the weekly discussions will be reported by the Champions. Feedback from the ICU teams on the report structure will be sought prior to and during implementation.

##### Strategy 3

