**Fig. 1 Fig1:**
[figure not shown]
Project timeline

At month 4, ICU teams will commence the protocolised review in their ICU. The Champion will have access to the online enhanced CQR reports, and the online education material will remain available to all ICU team members. Online support for troubleshooting relating to the implementation strategies will be available to the Champions. In addition, voluntary monthly group sessions will be facilitated by the project team from months 4–6, whereby Champions, RAs and other team members will be welcome to join to reflect on their experience and share learning between sites. Daily data collection (CQR and E-CRF) will continue throughout this period. Champions will be interviewed during months 4–6 to explore barriers and facilitators to implementation, adaptations made to both the intervention and its implementation, along with perceptions regarding likely adoption and maintenance (Supplementary File 3).

At the end of month 6, the implementation strategies of online education, the role of Champions, and the RA collecting daily data on review processes will cease. The daily auditing of whether reviews take place will be transferred to the CQR data collectors and reported monthly as part of the CQR report. A second interview will be conducted with Champions following month 6 to explore barriers and facilitators to adoption, and adaptations to the intervention made post-implementation (Supplementary File 4).

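### The audit-and-feedback meeting measure divides an uncapped count of meetings by a fixed 12, so extra meetings in some weeks can hide weeks with none and the score can pass 100%

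*Protocol article*

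**What the plan says.** The Fidelity row of Table 2 (protocol article, Statistics) adds a second measure to the review-based one: "Proportion of weekly A&F report meetings held from month 4 until the time of adoption (Number of meetings/12, expressed as a" percentage. It is marked "not in composite outcome" and, unlike the main Fidelity measure, carries no 80% threshold.

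The text on Strategy 2 (Implementation, Design) says that once the review begins, "frequency of reports will be increased to weekly (for a maximum of 3 months"). Champions are to encourage discussion of the report with the ICU team "at their preferred frequency and structure, but as a minimum weekly", and they report on these discussions.

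Three other places bear on the window:

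- Table 1 lists "Additional data collected for audit and feedback weekly during months 4–6".
- The Implementation procedure closes the support phase at one point for all sites: "At the end of month 6, the implementation strategies of online education, the role of Champions, and the RA collecting daily data" on review processes all stop then.
- The Adoption row of Table 2 is the "Proportion of prescriptions reviewed as intended during month 7", the same month for every ICU.

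**The concern.** The label and the formula describe different quantities. A proportion of weekly meetings held suggests a count of weeks, or of weekly reports, that led to a meeting. The formula instead counts meetings, and Strategy 2 allows more than one a week. Surplus meetings in busy weeks can then offset weeks with none. Such a score can stay between 0 and 100%, where nothing flags it. In other cases it passes 100%, which a proportion cannot do.

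The window has a separate fault. It ends at a time of adoption that the article does not define as an event or a date. The main Fidelity measure and the main Reach measure both state months 4–6 plainly; this one does not.

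What is at stake is a reported process measure. It is the only numerical measure in Table 2 of whether audit-and-feedback discussions took place, and audit and feedback is one of the three implementation strategies. A site that missed the weekly minimum for half the period could be reported as having delivered it in full.

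**Working it through.** **Inputs**

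- Formula: "Number of meetings/12, expressed as a" percentage (Table 2, Fidelity row).
- Meeting frequency: at least weekly, with more allowed (Strategy 2).
- Weekly reporting: months 4–6, for at most 3 months (Table 1; Strategy 2).
- Counting rule: the article states no cap and no limit of one meeting per week or per report.

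**Step 1. Reproduce the 12.** 3 months × 4 weeks = 12. By calendar, 3 × 365.25/12 ÷ 7 = 13.04 weeks (89 to 92 days give 12.7 to 13.1). So 12 is a rounded week count for months 4–6.

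**Step 2. Apply the formula, score = meetings ÷ 12.** The last column is the share of weeks with at least one meeting.

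| Pattern of meetings | Meetings | Score | Weeks with a meeting |
|---|---|---|---|
| Once a week, 12 weeks | 12 | 12/12 = 100% | 12/12 = 100% |
| Once a week, 13 weeks | 13 | 13/12 = 108.3% | 13/13 = 100% |
| Twice a week, 12 weeks | 24 | 24/12 = 200% | 12/12 = 100% |
| Three a week, 12 weeks | 36 | 36/12 = 300% | 12/12 = 100% |
| Twice a week for 6 weeks, then none | 12 | 12/12 = 100% | 6/12 = 50%, or 6/13 = 46% |

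The first and last rows matter most. Both score 100%, yet one site met the weekly minimum throughout and the other missed it for half the period. The meeting patterns are illustrations; the article gives no expected frequency above the minimum. The 108.3% is calendar rounding and carries little weight.

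**Step 3. Check the window.** Set side by side, the passages give a start at month 4, weekly data in months 4–6, an end of the Champion role at the end of month 6, and Adoption assessed in month 7 for all. The consistent reading is a common months 4–6 window, which also fits the 12. No passage says how or when an individual ICU would be declared to have adopted.

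**Step 4. Apply a week-based measure.** With weeks with at least one meeting ÷ weekly reports issued, a site meeting every week scores 100% whether 12 or 13 reports were issued. The site that stopped after 6 of 12 weeks scores 50%. If each week is matched to one report, the measure cannot exceed 100%.

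**The case against.** The strongest reply is that the unit named is the weekly report meeting. With one report a week, the natural count is one meeting per report, and further discussions would not be counted. A counting rule of this kind may sit in the full protocol or analysis plan, and the Statistics section promises published indicator definitions before data collection. Champions also describe the presence and structure of the discussions, so a site that met often and then stopped could be seen in that record. No planned analysis relates this measure to passing or failing the composite; determinants of implementation are studied through interviews and implementation logs.

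Most of this stands, and it limits the importance of the point. It does not remove it. The article does not leave the rule open: it prints numerator, window and denominator, and the printed numerator is the number of meetings. Followed literally beside the weekly minimum, it gives the results in the table.

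A reader might go further and infer that ICUs adopting quickly are penalised, because their window closes early while the denominator stays at 12. Perfect weekly attendance would then score 6/12 = 50% for a window closing at week 6, or 8/12 = 66.7% at week 8. The documents do not support this. It needs an adoption date for each ICU, and the plan has none; Adoption is a month-7 rate for all. The 3-month maximum on weekly reports leaves room for a shorter period, but no rule for stopping early is given. Those figures are hypothetical.

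**Conclusion.** The point holds as a small defect in how a descriptive measure is defined. On the literal formula, a site with meetings in only half the weeks can score 100%, and a site meeting more often than weekly can score 200% or more. This assumes that every meeting is counted, which is what the printed numerator says, and that some sites meet more than weekly, which Strategy 2 allows. How many will do so is not known from the article.

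The end of the window is ambiguous in wording, but the other passages point to months 4–6 for every site. The article gives no ground for claiming bias against early adopters, or that feedback would be made to look inversely related to success.

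The measure is outside the composite and has no threshold or planned test. No primary or secondary conclusion changes; the gain is a delivery figure that means what its label says.

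**What to change.** Change one line in the Fidelity row of Table 2:

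- State the window as months 4–6, as for the main Fidelity and Reach measures, and drop the reference to the time of adoption.
- Define the measure as the number of weeks in that window with at least one audit-and-feedback meeting, divided by the number of weekly reports issued to that ICU in the window. Match each week to one report so that the ratio stays within 100%.
- Drop the fixed 12.
- Report the total number of meetings separately, so that sites meeting more than weekly are still described.

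The cost is an edit. Champions already report the weekly discussions, and reports are generated centrally, so the number issued to each ICU should be known. No new data collection should be needed, provided that the Champions' reports can be assigned to a week.
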